### Data Managing

BBHI is an ICT-based study, where technology plays a key role in the collection and management of the data. The data generated via online questionnaires is transferred using secure procedures and stored in a cloud server, which assures full-time access to data as well as the necessary security protocols. Encrypted communication based on TLS (Transport Layer Security) is used whenever personal information is transferred between systems. The collected data are anonymized and kept confidential to protect the privacy of the participating users, fulfilling all the requirements stated by the Spanish Organic Law and EU regulations.

## Anticipated Results

### Limits of Detection and Statistical Analysis

#### Phases I and II

Considering the sample size of participants in phase I we calculated the relative risk of being exposed to a “brain health related” factor (or combination of factors) by comparing the estimated incidence rate of any neurological and neuropsychiatric diseases predicted in the Catalan population and the incidence predicted in a certain % of the cohort exposed to a protective factor (see Dartigues et al., 1992; Cyceron, 2003).

Assuming α risk of 0.05, a β risk of 20%, and a 5% per year drop out, after 5 years we will be able to identify a protective factor that represents a relative risk of 0.77, if 30% of participants are exposed to it. If the number of participants exposed is 20% the minimum relative risk identifiable is 0.73 and for an amount of 10% it is 0.66.

For the in person assessment (phase II), where 1,000 volunteers will be examined in-person, we will be able to detect a 0.61 relative risk if 30% of participants are exposed, 0.55 relative risk for 20% exposed, and 0.44 relative risk for 10% exposed.

Based on evidence from previous studies that look at the association between the reduction in the incidence of various neurological and neuropsychiatric diseases and different lifestyles these results indicate that at 5 years we will have sufficient power to detect factors related with brain health maintenance in our sample (La Rue, 2010; Baglioni et al., 2011; Kuiper et al., 2015; Frankish and Horton, 2017). Note however, that the main goal of the phase II of BBHI is descriptive, aiming for a deep phenotyping characterization of the biological markers of brain health.

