## Abstract

The Barcelona Brain Health Initiative (BBHI) is an ongoing prospective longitudinal study focused on identifying determinants of brain health. The main objectives are: (i) to characterize lifestyle, cognitive, behavioral and environmental markers related to a given individual’s cognitive and mental functions in middle to old age, (ii) to assess the biological determinants predictive of maintenance of brain health, and (iii) to evaluate the impact of a controlled multi-dimensional lifestyle intervention on improving and maintaining brain health. The BBHI cohort consists of >4500 healthy participants aged 40–65 years followed through online questionnaires (Phase I) assessing participants’ self-perceived health and lifestyle factors in seven different domains: overall health, physical exercise, cognitive activity, sleep, nutrition, social interactions, and life purpose. In Phase II a sub-group of 1,000 individuals is undergoing detailed in-person evaluations repeated at two-yearly intervals. These evaluations will provide deep phenotyping of brain function, including medical, neurological and psychiatric examinations, assessment of physical fitness, neuropsychological assessments, structural and functional brain magnetic resonance imaging, electroencephalography and perturbation-based non-invasive brain stimulation evaluations of brain activity, as well as collection of biological samples. Finally, in Phase III a further sub-group of 500 participants will undergo a similar in-person assessment before and after a multi-dimensional intervention to optimize lifestyle habits and evaluate its effects on cognitive and brain structure and function. The intervention group will receive remote supervision through an ICT-based solution, with the support of an expert in health and lifestyle coaching strategies aimed at promoting adherence. On the other hand, the control group will not have this coaching support, and will only receive education and recommendations about healthy habits. Results of this three-part initiative shall critically contribute to a better understanding of the determinants to promote and maintain brain health over the lifespan.

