**FIGURE 2 F2:**
[figure not shown]
Example of participants’ personal profile page and web-based questionnaires.

Upon recruitment to the study, and provision of the web-based informed consent, participants are asked to respond periodically to different questionnaires, that describe their self-perceived health and lifestyles in the 7 domains hypothesized to be related to brain health. These 7 “pillars of brain health” are overall physical/general health, nutrition, sleep, physical activity, cognitive activity, socialization and vital plan. Moreover, biographical and socio-demographical information, as well as other factors related to cognitive reserve, are collected. Furthermore, being based in the Catalan city of Barcelona, affords the study the possibility to study the specific contribution of bilingualism. We thus have the opportunity to study the specific contribution of some variables related with bilingualism (proficiency, age of acquisition, use, etc.) to cognitive reserve and brain health (Calabria et al., 2017).

The primary end point of participation in the study is the diagnosis of any brain (psychiatric or neurological) diseases. Therefore, participants are asked to report new diagnosis upon their appearance, and every year we query them for new diagnoses and about the number of times they have visited their GP.

A literature review of epidemiological data collected in Catalan, Spanish, and European populations regarding major neuropsychiatric diseases and compared with demographical characteristics of the BBHI participants, suggested that in 10 years almost one third of our cohort will be newly diagnosed with a neurological or psychiatric disease (see **Figure 3**; Von Campenhausen et al., 2005; Bermejo-Pareja et al., 2008; Garre-Olmo et al., 2010; Kirkbride et al., 2011; Pradas et al., 2013; Petersen et al., 2014; Vila-Corcoles et al., 2014). Consequently, affording us the possibility to study lifestyles and biological determinants of brain health with sufficient signal.

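### The Phase II detectable relative risks (0.61, 0.55, 0.44) do not fit the Phase I limits under the single set of assumptions given for both

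*Protocol article*

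**What the plan says.** The subsection Phases I and II, under Limits of Detection and Statistical Analysis, opens with its assumptions: "Assuming α risk of 0.05, a β risk of 20%, and a 5% per year drop out, after 5 years". Under these it gives minimum detectable relative risks for Phase I of 0.77, 0.73 and 0.66 when 30%, 20% and 10% of participants are exposed. It then turns to the 1,000 Phase II volunteers and, with no further assumption, says "we will be able to detect a 0.61 relative risk if 30% of participants are exposed, 0.55 relative risk for 20% exposed", and 0.44 for 10% exposed. Its conclusion covers both sets: "at 5 years we will have sufficient power to detect factors" related to the maintenance of brain health.

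The subsection gives no baseline incidence, formula, sidedness or numerical Phase I sample size. The nearest inputs elsewhere in the article are:
- Characterization of the Cohort: 4,206 active participants.
- Phase 1: Self-Report Online Questionnaires: the expectation that "in 10 years almost one third of our cohort will be newly diagnosed with a neurological or psychiatric disease".

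**The concern.** A detectable relative risk is fixed by the analysed sample, the incidence and the test. The Phase I and Phase II limits sit under one stated set of assumptions and differ only in the number of people, so either set should lead to the other. They do not: the Phase II limits look too favourable for 1,000 people who lose 5% a year.

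What is at stake is the claim of adequate power at 5 years as far as it covers Phase II. Principal Statistical Analysis plans odds, hazard and relative-risk analyses of the binary end point for both phases. On the Phase I basis, a lifestyle factor would have to be clearly more protective than printed to be found with 80% power in the in-person sample.

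**Working it through.** **Inputs.** Alpha 0.05 (taken as two-sided), power 0.80, 5% yearly drop-out and 5 years, all from Phases I and II. Retention is 0.95^5 = 0.774. Phase I: 4,206 × 0.774 = 3,255. Phase II: 1,000 × 0.774 = 774. Assumption: 5-year incidence in the unexposed p0 = 1/6, half of one third in 10 years.

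**Formula (pooled two-proportion test).** With exposed fraction e, p1 = RR × p0 and p̄ = (1−e)p0 + e·p1, the total number needed is

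N = [1.96·√(p̄(1−p̄)(1/e + 1/(1−e))) + 0.842·√(p1(1−p1)/e + p0(1−p0)/(1−e))]² / (p0−p1)²

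**Step 1: reproduce Phase I.** For e = 0.30 and RR = 0.77: p1 = 0.1283, p̄ = 0.1552, N = 3,248, against 3,255 available. Solving for RR at N = 3,255 gives 0.770, 0.737 and 0.654, against the printed 0.77, 0.73 and 0.66. The article's own inputs with p0 = 1/6 therefore recover Phase I closely. Solving instead for the incidence that returns each printed Phase I limit gives 0.166, 0.159 and 0.172.

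**Step 2: apply the same inputs to Phase II (p0 = 1/6).**

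| | 30% exposed | 20% | 10% |
|---|---|---|---|
| Printed limit | 0.61 | 0.55 | 0.44 |
| Pooled, 774 retained | 0.551 | 0.489 | 0.339 |
| Pooled, 1,000 retained | 0.600 | 0.544 | 0.408 |
| Arcsine, 774 retained | 0.561 | 0.506 | 0.375 |
| Arcsine, 1,000 retained | 0.608 | 0.558 | 0.436 |

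The printed values lie near the rows without drop-out and away from the rows with it.

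**Step 3: a check that does not rest on the assumed incidence.** If both phases share the same drop-out, retention cancels and the samples must stand in the ratio 4,206/1,000 = 4.21. The ratio implied by the printed pairs (0.77 with 0.61, 0.73 with 0.55, 0.66 with 0.44) is N(Phase I)/N(Phase II). With the pooled formula at p0 = 1/6 it is 3,248/1,056 = 3.08, 3,071/1,027 = 2.99 and 3,385/1,137 = 2.98. For incidences from 5% to 33%:

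| Formula | Implied ratio |
|---|---|
| Log relative risk | 2.44-2.97 |
| Pooled | 2.94-3.10 |
| Arcsine | 3.02-3.20 |
| Unpooled | 3.20-3.77 |
| Schoenfeld (events) | 3.39-3.81 |

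None reaches 4.21. In every row except the pooled one, alpha and power enter only through a common factor that cancels, so sidedness does not matter there. With the most favourable rounding of both printed values at incidence 1/6, the largest ratio is 4.06 (Schoenfeld, 10% exposed). Drop-out in Phase I only would require 3,255/1,000 = 3.26, which lies inside the range.

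**Step 4: power at the printed Phase II limits with 774 retained, p0 = 1/6.**

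| Formula | 30% | 20% | 10% |
|---|---|---|---|
| Pooled | 66.0% | 66.6% | 59.4% |
| Arcsine | 68.7% | 71.0% | 68.5% |
| Log relative risk | 62.3% | 60.5% | 51.1% |
| Schoenfeld | 67.6% | 73.6% | 77.6% |

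With 1,000 retained, the pooled figures are 77.7%, 78.8% and 73.5%.

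The unpooled formula needs a note. At p0 = 1/6 and 10% exposed it requires 7.849 × (0.0680/0.1 + 0.1389/0.9)/0.0933² ≈ 751 people, so 774 would just suffice. But at that incidence it also needs only about 2,770 for the Phase I limit, against 3,255 available, so 1/6 does not fit Phase I under that formula. At the incidences that do fit (0.158, 0.144, 0.144), its Phase II power is about 70%, 71% and 75%.

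**The case against.** **The inputs are not all stated.** The subsection does not say that 4,206 was used, and that figure is a count to date of a cohort still recruiting. With drop-out kept in both phases, about 3,000 Phase I participants and an incidence near 0.22, the pooled formula gives 0.77/0.74/0.65 for Phase I and 0.61/0.56/0.43 for Phase II, close to all six printed values. This stands as a reason not to assert the cause. It does not rescue the text, because the article states neither number, and a Phase I sample above 4,206 widens the gap.

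**The incidence is assumed.** The expected survival curve (Figure 3) is not shown here. A constant hazard gives 1 − (2/3)^0.5 = 18.4% at 5 years, and pooled power is then about 71%, 72% and 66%. At 22% it is 81%, 82% and 77%. So the size of the shortfall is conditional. But with 4,206 participants, 22% would put the pooled Phase I limits at 0.805, 0.777 and 0.705, not the printed ones.

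**Phase II may have its own incidence.** It takes 500 people from each extreme of the mental-health score (Sub-cohort Selection Criteria). An incidence of 0.21-0.23 would produce the printed limits with drop-out included (pooled formula). This is possible but undeclared.

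**The method may be one-sample.** The text describes comparing the exposed with a population rate. At 1/6, that version gives about 81%, 76% and 64%. Once its incidence is fitted to the Phase I limits, power falls to about 60-64%, so the inconsistency remains.

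**The consequence is limited.** The article calls Phase II mainly descriptive, and its size comes from the 500 + 500 selection. This holds, and it lowers the priority of the point.

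**Conclusion.** Wrong as written; should be fixed. With 4,206 and 1,000 participants and a common incidence and drop-out, the printed Phase I and Phase II limits cannot both hold: the pairs imply a sample ratio of about 2.4-3.8, against 4.21. If the Phase I assumptions apply to Phase II with drop-out, power at the printed limits is below 80%. It is about 59-67% with the pooled formula and an assumed 5-year incidence of 1/6. It is about 51-78% across two-sided two-group formulas, taken at that incidence or, for the unpooled formula, at the one that fits Phase I.

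A reader might infer three stronger things that the article does not support.
- That drop-out was certainly left out of Phase II. This is the simplest explanation, but the pooled match without drop-out is loose at 10% exposed (0.41 against 0.44), and a higher incidence would serve as well.
- That Phase II power simply is 60-67%. That band belongs to one formula and one assumed incidence.
- That the abstract's cohort size ("The BBHI cohort consists of >4500 healthy participants aged 40–65 years") supports the point. The 4,757 enrolled less 189 and 362 excluded leave 4,206, so the abstract does differ from the text, but this is a separate reporting discrepancy with no bearing on the Phase II limits.

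**What to change.** Recompute the three Phase II limits with the same incidence, formula and drop-out as Phase I, or state that the printed values assume no drop-out over 5 years or a different incidence, and justify that choice. For illustration only, the recomputed limits would be about 0.55/0.49/0.34 with the pooled formula and incidence 1/6, or about 0.56/0.51/0.38 with arcsine. The final values should come from the sponsor's own inputs. Give the 5-year incidence, the formula with its sidedness, and the retained number for each phase, and limit the statement on power at 5 years to what the corrected Phase II figures support.

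The cost is three numbers, a sentence or two of assumptions, and less favourable Phase II figures. The design and the Phase II sample size need not change.

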In recent years a major focus has been placed on the discovery and validation of new ‘biomarkers’ for major diseases (Olsson et al., 2016 for a recent review and meta-analysis) that allow the identification of ‘at risk’ individuals, or even subjects at ‘preclinical stages’ of diseases, years before the possible manifestation of clinical symptoms (e.g., Dubois et al., 2007). It is now well-accepted that structural and functional brain changes associated with the development of neurodegenerative diseases can begin some 10–20 years prior to the onset of symptoms (Beason-Held et al., 2013). During this “pre-clinical period,” individual differences in brain resilience may delay the appearance of symptoms or act to reduce or eliminate the clinical and behavioral impact of pathologies (Nyberg et al., 2012). For this reason, there is a strong need to focus research on such factors that could prevent illness and promote brain resilience in the presence of pathology. For example, in the case of dementia, delaying the onset of symptoms for just 1 year could prevent disability in over 11.8 million cases in the next 30 years representing a cost savings of $219 billion (Brookmeyer et al., 2007; Zissimopoulos et al., 2015).

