#### Characterization of the Cohort

Barcelona Brain Health Initiative study participants are community-dwelling individuals between 40 and 65 years of age, of both sexes, free from any self-reported neurological or psychiatric diagnosis at the time of recruitment. As of the end of June 2018, 4,757 participants have enrolled in the project via the web-based application and completed the first on–line questionnaire. Of these, 189 subjects were excluded because they reported to be less than 40 years old or older than 65 years. Another 362 subjects reported to have been diagnosed with neurologic or psychiatric disease, including Alzheimer’s disease, Parkinson’s disease, multiple sclerosis, amyotrophic lateral sclerosis, cerebral stroke, schizophrenia, or major depression. Accordingly, 4,206 participants (2,792 women) are active participants in the study to date. Mean age ± standard deviation of the participants is 52 ± 7 years with an age distribution that is highly representative of the Catalan population. The cohort does, however, include an over-representation of women (66%), and participants have overall a higher education level than the general population (70% have advanced studies, bachelor degree equivalent or higher). The socio-demographic information of currently enrolled participants is summarized in **Table 1**.

**Table 1 T1:** Demographic characteristics of currently enrolled participants.

	Men	Women	

	***Mean (SD)***	***Mean (SD)***	***p*-value**
Age (years)	52.8 (7.3)	52.0 (7.3)	<0.01^∗^

	**Men**	**Women**	**Total**

	***N (%)***	***N (%)***	***N (%)***

Participants	1414 (33.4)	2792 (66.6)	4206 (100)

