#### Principal Statistical Analysis

Principal statistical analyses to be performed will include mainly linear regression models in within-subjects and between-groups experimental designs. We may require applying non-parametric statistics in certain cases.

We will also use exploratory data mining techniques like clustering and classifiers in order to identify groups of similar participants and explore the relation between different biologic and lifestyles variables and the different outcomes.

The final aim of this study is to investigate and identify those factors that can promote Brain Health. Considering the binary nature of the end-point of this study (phase I and II), the analysis within the study population will be based on the calculation of odds ratios, hazard ratios and relative risks of exposure to protective factors on the *a priori*-defined 7 pillars of interest. All analyses will be performed correcting for covariate variables (e.g., age, sex, education, income, etc.)

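### The 5-year claim to identify protective factors rests on counting diagnoses from enrolment, so undetected early disease may bias associations toward apparent protection; a lagged sensitivity analysis would show how far

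*Protocol article*

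**What the plan says.** Under Limits of Detection and Statistical Analysis, Phases I and II, the article sets its inputs: "Assuming α risk of 0.05, a β risk of 20%, and a 5% per year drop out". After 5 years the study should identify a protective factor with a "relative risk of 0.77, if 30% of participants are exposed to it". It adds: "If the number of participants exposed is 20% the minimum relative risk identifiable is 0.73 and for an amount of 10% it is 0.66". It concludes that "these results indicate that at 5 years we will have sufficient power to detect factors related with brain health maintenance in our sample".

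Four other places bear on this:

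- **Introduction:** "structural and functional brain changes associated with the development of neurodegenerative diseases can begin some 10–20 years prior to the onset of symptoms". The rationale for the Phase III intervention repeats that brain changes start decades before symptoms.
- **Characterization of the Cohort:** participants are "free from any self-reported neurological or psychiatric diagnosis at the time of recruitment". Undiagnosed disease is not screened out.
- **Phase 1: Self-Report Online Questionnaires:** the primary end point is any new psychiatric or neurological diagnosis, and almost one third of the cohort is expected to have one within 10 years.
- **Principal Statistical Analysis:** odds ratios, hazard ratios and relative risks are planned for protective factors in the seven pillars, with adjustment described as "All analyses will be performed correcting for covariate variables (e.g., age, sex, education, income, etc.)". No lag or exclusion of early diagnoses is mentioned.

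The section on pitfalls covers drop-out, instructor bias and representativeness. It does not mention reverse causation.

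**The concern.** If disease is under way but undiagnosed when a participant first reports diet, sleep, activity, social contact or purpose, a poor habit may be a result of the disease and not a cause. Such a person enters the cohort, counts as unexposed, and becomes a case within a few years. Healthy habits then appear protective even if they do nothing, so the bias runs in the direction of the hoped-for finding.

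The article gives some support for such overlap outside neurodegeneration. In Sub-cohort Selection Criteria it links low self-rated mental health scores with anxiety, depression, fatigue, physical functioning and satisfaction with social participation. That is an association, with no time order stated, but several of these domains are close to the pillars used as exposures.

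Identifying factors that promote brain health is the study's declared final aim. Calling an unlagged 5-year association protective could therefore bias its main conclusion.

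**Working it through.** **1. Reproducing the stated limits.**

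Inputs from the article: N = 4,206; drop-out 5% per year; α = 0.05 (taken as two-sided); power 80%; exposed share 30%, 20% or 10%.

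Assumed: a 5-year risk in the unexposed of 1/6, half of the 10-year one third. The article's text gives no 5-year risk.

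Retained: 4,206 × 0.95^5 = 3,254. The detectable relative risk is the value at which a pooled-variance two-proportion test has 80% power.

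| Exposed | Stated RR | Recomputed RR | Power at stated RR |
|---|---|---|---|
| 30% | 0.77 | 0.770 | 80.1% |
| 20% | 0.73 | 0.737 | 82.4% |
| 10% | 0.66 | 0.654 | 78.3% |

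A constant-hazard risk, 1 − (2/3)^0.5 = 18.35%, fits less well (0.782, 0.751, 0.672). The published limits thus match a calculation that counts diagnoses over the whole 5 years from enrolment.

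**2. Cost of leaving out early diagnoses.**

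Assume uniform incidence of 1/30 of the baseline cohort per year. With a lag of L years:

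- number still at risk = 3,254 × (1 − L/30)
- risk in the remaining window = ((5 − L)/30)/(1 − L/30)

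For L = 2 this gives about 3,037 people and a risk of 0.100/0.933 = 0.107, so about 325 diagnoses. That is 60% of the unlagged 542.

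| Lag | Diagnoses | Detectable RR (30/20/10% exposed) | Power at the stated RRs |
|---|---|---|---|
| 0 | 542 | 0.770 / 0.737 / 0.654 | 80% / 82% / 78% |
| 1 year | 434 | 0.741 / 0.704 / 0.610 | 69% / 71% / 66% |
| 2 years | 325 | 0.699 / 0.656 / 0.549 | 55% / 57% / 51% |
| 3 years | 217 | 0.631 / 0.579 / 0.451 | 38% / 39% / 33% |

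**3. Possible size of the bias when the true relative risk is 1.**

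Let e be the exposed share of the cohort, f the share of 5-year cases already prodromal at baseline, and k the proportional drop in exposure among them. Neither f nor k is in the article. With x = f × k, the exposed share among cases is e(1 − x), and

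apparent RR = (1 − x)(1 − e) / (1 − e(1 − x)).

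For e = 0.30:

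| f | k | x | Apparent RR |
|---|---|---|---|
| 5% | 50% | 0.025 | 0.975 × 0.70 / 0.7075 = 0.965 |
| 10% | 50% | 0.05 | 0.95 × 0.70 / 0.715 = 0.930 |
| 50% | 30% | 0.15 | 0.85 × 0.70 / 0.745 = 0.80 |
| 50% | 50% | 0.25 | 0.75 × 0.70 / 0.775 = 0.68 |

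In the first two rows a falsely significant protective result would occur about 6% and 13% of the time, against a nominal 2.5%. For the bias alone to equal the stated limits, x must be 0.17, 0.23 and 0.32 at 30%, 20% and 10% exposed.

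**The case against.** The strongest reply is that this is a condensed article. Lags and sensitivity models commonly sit in an analysis plan, which is not shown, so their absence is no error. That stands. What remains is the article's own 5-year statement: under the assumptions in the working, a lag added elsewhere would shift the published detection limits.

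A reader might infer more than the text supports:

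- **That all 5-year cases fall inside a 10–20-year preclinical period.** The Introduction says neurodegenerative changes *can* begin that early. The end point is any psychiatric or neurological diagnosis, and no latency is given for the other diseases and no neurodegenerative share.
- **That early disease will lower the habits.** The article never says so; it *may*. With few prodromal cases the bias is small.
- **That baseline symptoms are excluded from adjustment.** The covariate list is illustrative and open-ended, so not naming them is only missing detail.
- **That the study cannot separate cause from consequence.** Questionnaires are repeated, a 10-year horizon is projected, and the randomised Phase III does not share this bias for its own outcomes.

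It is also fair to say that a 2-year lag does not span a 10–20-year preclinical period, and that the concluding power sentence speaks only of related factors. The same section, however, also speaks of protective factors.

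**Conclusion.** The point holds in a limited form. The article says that 5 years of follow-up can identify protective factors, using limits that match counting diagnoses from enrolment. Its own account of disease onset, and an entry rule based only on self-reported diagnoses, leave room for reverse causation in an unknown share of those diagnoses.

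The direction is toward apparent protection. At 30% exposed, the apparent relative risk for a habit with no effect ranges from about 0.97 to 0.68, depending wholly on assumed values of f and k. The low end is modest, and the high end is as large as the effects the study is sized for. The documents do not show which applies, so neither a certain nor a dominant bias can be claimed.

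The detection limits rest on the assumed 1/6 risk, and the lagged limits also on uniform incidence. This is a worthwhile, inexpensive improvement to the analysis and its wording, not a defect that invalidates the cohort.

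**What to change.** **In Principal Statistical Analysis**, add a prespecified sensitivity analysis for each pillar:

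- Leave out diagnoses in the first 2 years, and set the estimate and confidence interval beside those of the main analysis.
- Repeat at 10 years with a longer lag.
- Alongside it, report a second model adding the baseline depression and anxiety, Neuro-QoL cognitive function and PROMIS mental-health scores, which the first questionnaire already collects.

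**In Limits of Detection and Statistical Analysis, Phases I and II**, describe the 5-year results as associations. State that the lagged 5-year limits are about 0.70, 0.66 and 0.55 at 30%, 20% and 10% exposed (1/6 five-year risk, uniform incidence), against 0.77, 0.73 and 0.66.

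**Cost.** No new data are needed. The 2-year lag keeps about 60% of the diagnoses, and power at the stated relative risks falls to 55%, 57% and 51%. The symptom-adjusted model may remove part of a true effect. Both analyses should therefore support the main one, and neither should be a pass/fail condition for reporting a factor. Agreement between lagged and unlagged estimates at 5 years would be reassuring, but would not rule out reverse causation over 10–20 years.
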